## 3. Discussion

This study protocol describes the hybrid design of an effectiveness-implementation study that takes an innovative method by examining the recruitment success of two implementation approaches (i.e., a mass media approach and a health care approach) to test the (cost)effectiveness of a proactive telephone counseling program for smoking parents of children aged 0–18 years. By evaluating the different implementation approaches and their effect on the (cost)effectiveness, this study aims to provide more insight into how this smoking cessation program can be efficiently and sustainably implemented in The Netherlands. Based on earlier results of Schuck et al., 2014 [14], it is hypothesized that the cessation rates of parents who receive telephone counseling will be higher at three months post-intervention compared to the cessation rates of parents who receive a self-help brochure. In addition, it is expected that (youth) health care professionals will be a more promising implementation approach for connecting smoking parents with the telephone counseling compared to (online) mass media because most parents are motivated to quit and find it acceptable to be directed to telephone counseling when their child’s health is concerned [11,34].

### Strengths and Limitations

A strength of this study is that the Russell Standard (Clinical) version 2 [47] will be used to assess smoking cessation. It provides standard criteria of successful smoking cessation rates to enable meaningful comparisons between different studies [47]. Another strength is that as an effectiveness and an implementation study, it allows for the identification of important implementation strategies and interactions, offering valuable information to decision-makers [41,42]. In addition, a mixed-method design (i.e., quantitative and qualitative research) yields stronger evidence because of convergence and confirmation of the results [55]. In accordance with Schuck et al., 2014 [14] some secondary outcomes will be included. However, our power calculation was only based on the primary outcome. Another limitation is that we will not be able to assess smoking cessation rates with a long term assessment (e.g., one year follow up). However, in accordance with Schuck et al., 2014 [14] we have a follow-up assessment at three months. In addition, we will use the Russell Standard (Clinical) version 2 [47] to assess smoking cessation rates. Therefore, we are able to compare our smoking cessation rates with that of other studies. Finally, smoking cessation will be measured using self-reports, which may lead to an under-reporting due to the social desirability bias [56]. To verify this potential bias, we will inform parents in the introduction of the second questionnaire that a random subsample of parents (30%) will be approached for biochemical validation (NicAlert dipstick (Nyomax, Hasbrouck Heights, NJ, USA).

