The existing research suggests that most parents want to quit smoking and even tried to quit smoking [10]. In addition, most parents would accept smoking cessation support, such as telephone counseling [11]. A review consisting of 77 (quasi) randomized controlled trials (RCT) on telephone counseling confirmed that telephone counseling is effective in increasing smoking cessation rates [12]. Moreover, Hollis et al., 2007 [13] found that telephone counseling is cost-effective (i.e., the degree to which something is effective in relation to its costs). Recently, a tailored telephone counseling program for smoking parents was tested in The Netherlands [14]. Parents who smoke (*N* = 512) were recruited in an RCT and assigned to the intervention condition (i.e., tailored telephone counseling and supplementary materials) or the control condition (i.e., a standard self-help brochure). Parents who received telephone counseling were more likely to report 7-day point prevalence abstinence at three months post-intervention (44.5% versus 12.1%; OR = 6.89, 95% CI = 4.18–11.36) and to use nicotine replacement therapy (48.4% versus 20.9%) compared to parents who received a standard self-help brochure. Among parents who did not quit smoking, those who received telephone counseling were more likely to make a quit attempt (85.2% versus 68.1%) and to implement a complete home smoking ban (39.5% versus 26.1%) compared to parents who received the self-help brochure. Altogether, this study provided evidence that telephone counseling tailored to smoking parents is effective in helping parents quit smoking and developing parenting practices that protect their offspring from ETS exposure [14].

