### 2.7. Sample Size

Based on the results of Schuck and colleagues (2014) [14], our power calculation (Stata 12.1, StataCorp., College Station, TX, USA) indicated that 72 parents per implementation approach (36 intervention and 36 control) is sufficient to detect 7-day prevalence abstinence at three months post-intervention with a large effect (*p*_1_ = 0.445, *p*_2_ = 0.121, Power = 0.80, α = 0.05). Because we want to examine differences in smoking cessation rates between the two implementation approaches, we have to double from 72 to 144 parents. Based on the drop-out rates at 3-month follow-up of Schuck et al., 2014 [14] (i.e., 10% in the control group and 3.9% in the intervention group), we will anticipate 10% drop-out. This means that we will aim to recruit a minimum of 158 participating parents in total.

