### 2.8. Outcomes

The primary outcome measure will be 7-day point prevalence abstinence at three months post-intervention. In addition, secondary outcome measures include: (1) occurrence of at least 24 h of abstinence at three months post-intervention; (2) increase in motivation to quit; (3) number and duration of quit attempts; (4) use of and adherence to nicotine replacement therapy; (5) implementation of smoking restrictions at home; and (6) change in smoking-related cognitions (e.g., social norms, attitudes towards smoking, and self-efficacy). Moreover, to compare the success rates in this study with other studies, one outcome of the Russell Standard (Clinical) version 2 [47] will also be included as a secondary outcome (i.e., 14-day point prevalence abstinence at 4 weeks after the designed quit date).

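### Drawing the 30% biochemical validation sample from all parents sends about 34 of 47 approaches to self-reported smokers and only about 13 to reported quitters, so false claims of abstinence are checked very imprecisely

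*Protocol article*

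**What the plan says.** Section 2.8 fixes the primary endpoint: "The primary outcome measure will be 7-day point prevalence abstinence at three months post-intervention". Under Strengths and Limitations the article states that "smoking cessation will be measured using self-reports, which may lead to an under-reporting due to the social desirability bias". (For abstinence the bias runs towards over-claiming, so the phrase is right only if it means under-reporting of smoking.) As the safeguard, the introduction to the second questionnaire will tell parents that "a random subsample of parents (30%) will be approached for biochemical validation" with a nicotine dipstick. The stated purpose is to verify the potential bias. Nothing restricts or weights the subsample to parents who report abstinence.

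The planning rates are in section 2.7 ("0.445, *p*_2_ = 0.121, Power = 0.80, α = 0.05"). They come from the earlier Dutch efficacy trial described in the Introduction, where counselled parents were "more likely to report 7-day point prevalence abstinence at three months post-intervention (44.5% versus 12.1"%).

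**The concern.** Social desirability leads people who still smoke to say they have stopped. Only a claim of abstinence can be false in that direction, so tests on parents who admit smoking contribute little to estimating the bias. A simple random sample of parents takes claimants only in proportion to their share, which is well under half at the planning rates.

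Parents know whether they received up to six calls or a brochure, so the pressure to report success may differ between arms. The same self-reported outcome also supplies the incremental effect in the cost-effectiveness ratio (section 2.9). If false claims occurred, this check is the only safeguard the article names, and it would rest on a handful of tested quitters.

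**Working it through.** **Inputs**
- Rates 0.445 and 0.121, power 0.80, alpha 0.05; "72 parents per implementation approach (36 intervention and 36 control"); doubled to 144; 10% drop-out; 158 in total (section 2.7).
- Validation share 0.30, drawn from parents (Strengths and Limitations).

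**The plan's own sample size reproduces**
- Two-sided comparison of two proportions: [1.96 × √(2 × 0.283 × 0.717) + 0.8416 × √(0.445 × 0.555 + 0.121 × 0.879)]² / 0.324² = 29.1, so 30 per arm.
- With the continuity correction: (29.1/4) × [1 + √(1 + 4/(29.1 × 0.324))]² = 35.0, rounded up to 36 per arm, as stated.
- 2 × 36 = 72; 2 × 72 = 144; 144 × 1.10 = 158.4, stated as 158.

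**Where the approaches fall (158 parents, 79 per arm)**
- Approaches: 0.30 × 158 = 47.4.
- Expected reported quitters: 79 × 0.445 = 35.2 counselling; 79 × 0.121 = 9.6 control; total 44.7 (28.3% of 158).
- Reported quitters approached: 0.30 × 44.7 = 13.4 (10.5 counselling, 2.9 control).
- Self-reported smokers approached: 47.4 − 13.4 = 34.0, or 71.7% of approaches. Some 70% of quit claims are not checked.
- After 10% drop-out (142 parents): 42.6 approaches, 40.2 reported quitters, 12.1 of them approached.

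**Precision, if everyone approached is tested**
- Number of control quitters approached, binomial with n = 79 and probability 0.30 × 0.121 = 0.0363: none with probability 0.05, two or fewer with probability 0.45.
- Exact 95% upper limit for the misreporting rate when no test fails, 1 − 0.025^(1/n): n = 3, 71%; n = 13, 25%; n = 45, 8%.
- If 10% of claims are false (assumption), the chance of finding none is 0.9^13 = 0.25 against 0.9^45 = 0.009.

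**The same number drawn from reported quitters**
- 47.4/44.7 = 1.06 approaches per expected quitter; after drop-out 42.6/40.2 = 1.06.
- Allowing for chance in the number of quitters (simulation, 47 tests, full uptake): mean coverage 98%, 2.5th percentile 85%, probability of covering all about 0.70.
- Other quit rates, with reported quitters = 79 × (sum of the two rates):

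| Counselling v control | Reported quitters | Share of random approaches going to smokers | Coverage with 47 targeted tests |
|---|---|---|---|
| 30% v 12.1% | 33 | 79% | 100% |
| 44.5% v 12.1% | 45 | 72% | 100% |
| 50% v 15% | 51 | 68% | 92% |
| 55% v 20% | 59 | 63% | 79% |

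**What targeting does not buy**
- With 35 counselling and 10 control quitters all tested, two-sided Fisher power at 5% to detect a difference in misreporting (assumed rates) is about 1% for 20% v 10%, 13% for 30% v 10%, and 36% for 40% v 10%.
- If 1 of 10 control quitters failed, the exact 95% interval would be 0.3% to 44.5%.

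**The case against.** The case for leaving the plan alone has several parts.

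**Deterrence.** The notice reaches every parent before they answer, so it may discourage false claims whoever is tested later. Under random selection the chance of an approach does not depend on the answer. If parents are told that claimed quitters may be tested, reporting smoking becomes a way to avoid the test, and a genuine quitter who dislikes testing might take it. This stands as a real cost. It is modest, because a truthful notice can remain and a false claimant's chance of being approached rises from 30% to nearly 100% at the planning rates. It does not make the random frame suitable for estimating the bias it is meant to verify.

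**Tests on smokers have some value.** The trial admits parents who smoke only weekly (section 2.3), and testing admitted smokers would show whether the dipstick detects smoking in this population. A reader might infer that about 34 approaches are simply wasted. That goes too far: they say little about false quit claims, but not nothing about the test.

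**Comparison by arm.** A reader might infer that targeting would reveal misreporting that differs between arms. It would not do so reliably: about 10 control quitters are too few even if all are tested.

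**Unstated use of the results.** A reader might count it as a fault that the article does not say how test results enter the effectiveness estimate. That detail is commonly left to the full protocol or analysis plan, neither of which is shown, so it is no finding. The full protocol might also define the subsample more narrowly; the published wording, however, names parents as the frame.

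**Approaches are not completed tests.** Refusals reduce the verified number under either scheme. This stands, and every coverage figure here is a ceiling.

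**Conclusion.** The point holds as an inefficient design choice with a cheap remedy. It is not a contradiction, nor evidence that the primary result will be biased. At the planning rates, about 72% of some 47 approaches go to parents who already report smoking. About 13 of roughly 45 quit claims are checked, about 3 of them in the control arm. Overall misreporting would be estimated very imprecisely, and control-arm misreporting hardly at all.

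This rests on the rates in section 2.7, equal arms of 79, and reading the subsample as a simple random draw from all parents. Lower quit rates in practice would worsen the imbalance and make targeting easier. Rates well above plan would leave some claims unchecked under targeting (79% coverage at 55% v 20%), still far above 30%. That all claims would be verified cannot be promised: the chance is about 0.70 at the planning rates, even with full uptake.

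**What to change.** - Keep about 47 approaches, but draw them from parents in both arms who report 7-day abstinence at the second assessment. Take all of them if they number no more than about 47; otherwise take a random sample of them.
- Keep an advance notice in the questionnaire introduction, reworded so that it is true under the new selection.
- Report approaches, completed tests, refusals and failures, overall and by arm, and present the comparison by arm as descriptive.
- Record nicotine replacement use at the time of the test. In the earlier trial, counselled parents were more likely "to use nicotine replacement therapy (48.4% versus 20.9"%).
- Add a sensitivity analysis of the primary outcome that counts failed claims as smoking, shown with and without positive tests in current nicotine replacement users. The assumption is that such use can turn a nicotine dipstick positive. If it can, counting every failure as smoking would reclassify true quitters more often in the counselling arm.

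**Cost.** No additional approaches. The notice changes, which may need to be notified to the ethics committee. Approaches must wait for the returned questionnaire, selection depends on the answer given, and admitted smokers are no longer tested.

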## 4. Conclusions

The results of this study will reveal whether the telephone counseling is effective in “real life” conditions. If the counseling will not be as strong as we expect we will search for reasons and try to clarify why our results do not correspond to the results of Schuck et al., 2014 [14]. Consequently, we will think about how the telephone counseling can be improved. The results of Hayes et al., 2017 [57] could be important and relevant suggestions for the improvement of the telephone counseling. This study will also provide information on how and where to implement the telephone counseling for smoking parents in the most optimal manner in The Netherlands. If all four implementation channels will turn out successful in recruiting smoking parents (i.e., high recruitment rates and similar costs/participant), we will be able to conclude that a combination of all four implementation channels should be used to implement the telephone counseling. In contrast, if only one implementation channel turns out to be unsuccessful (i.e., extremely low recruitment rates and/or low quit rates), this particular channel should not be used to implement this program.

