### 2.2. Participants and Recruitment

In total, 158 smoking parents will be recruited through four different implementation channels (i.e., primary schools, online mass media, health care, and youth health care), which will be distinguished as two different implementation approaches (mass media approach and health care approach).

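### The Conclusions let low quit rates alone rule out a single recruitment channel, but quit rates are powered and compared only at approach level, leaving about 18 counselled parents per channel

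*Protocol article*

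**What the plan says.** Section 4 (Conclusions) sets out what will follow for implementation. If all four channels succeed, judged by recruitment rates and cost per participant, all four should be used. The next sentence covers the opposite case: "if only one implementation channel turns out to be unsuccessful", explained as "extremely low recruitment rates and/or low quit rates), this particular channel should not be used to implement this program". The joining words are *and/or*, so low quit rates suffice without poor recruitment. No threshold, comparator, arm or test is attached.

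Section 2.2 states that "In total, 158 smoking parents will be recruited through four different implementation channels", two channels to each approach. Section 2.7 sizes the trial by approach: "72 parents per implementation approach (36 intervention and 36 control"), doubled to 144 so that the two approaches can be compared, and raised to 158 for 10% drop-out. Section 2.10 plans logistic regression of cessation, then moderation and multi-group testing between recruitment approaches. It describes no comparison of quit rates between channels. Section 2.6 stratifies randomization by channel but sets no quota per channel.

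**The concern.** A stated consequence, not using a channel, hangs on a quantity that the design was not sized to estimate. Each approach is split into two channels, so a channel has about half the parents for whom power was calculated. With so few, the lowest of four quit rates can sit visibly below the rest by chance, and a channel that works as well as the others could be recommended against. The reverse error is also possible: a truly poor channel may not stand out.

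The two sentences in the Conclusions are also uneven. Success is judged on recruitment and cost, while failure adds quit rates. A channel that recruits well at similar cost but shows a low quit rate meets both descriptions.

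**Working it through.** **Inputs.** Rates of 44.5% (counselling) and 12.1% (brochure), from the earlier efficacy trial cited in Section 1 ("44.5% versus 12.1%; OR = 6.89, 95% CI = 4.18–11.36") and used in Section 2.7 ("0.121, Power = 0.80, α = 0.05"). Seventy-two evaluable parents per approach, 144 in total, two channels per approach. Assumption: equal recruitment across channels.

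**1. The plan's own figure.** Two-sided α = 0.05, power 0.80, mean rate (0.445 + 0.121)/2 = 0.283, difference 0.324:

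n = [1.960·√(2·0.283·0.717) + 0.842·√(0.445·0.555 + 0.121·0.879)]² / 0.324² = 29.1, i.e. 30 per arm.

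With the continuity correction, (29.1/4)·[1 + √(1 + 4/(29.1·0.324))]² = 35.04, i.e. 36 per arm. The stated 36 + 36 per approach is reproduced.

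**2. Size of a channel.** 144/4 = 36 evaluable parents, 18 per arm. Counting everyone randomized, 158/4 = 39.5, about 20 per arm.

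**3. Precision of a channel's counselled quit rate.** 1.96·√(0.445·0.555/18) = 0.23, or 23 points either side. For 8 quitters of 18 the exact 95% interval is 22% to 69%.

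**4. Four equally effective channels.** Simulation, 1,000,000 trials. The gap is the mean of the other three channels minus the lowest.

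| Quit rate used | Mean gap | ≥15 points | ≥20 points | ≥30 points |
|---|---|---|---|---|
| Counselled, 18 per channel | 16 points | 46% | 29% | 4% |
| Counselled, 20 per channel | 15 points | 50% | 26% | 4% |
| Both arms pooled (18 at 44.5% + 18 at 12.1%) | 9.5 points | 11% | 2% | under 0.1% |

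Fixed cut-offs for the counselled rate at 18 per channel: at least one of the four falls to half the true rate or below in 17% of trials (8% with 20 per channel), and to 12.1% or below in about 1%.

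**5. If *low* means no significant counselling effect within the channel.** Power at 18 per arm for 44.5% v 12.1% is 58% by normal approximation (60% exact chi-square, 46% Fisher). The chance that at least one of four equally effective channels fails is 1 − 0.584⁴ = 88% (87% to 96% across the three methods). The chance that exactly one fails is 4·0.416·0.584³ = 33% (21% to 34%).

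**6. Detecting a truly poor channel.** One channel at 22.25% (18 counselled) against 44.5% in the other three (54 counselled), two-sided pooled z-test by exact enumeration: power 39%.

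**The case against.** The sentence is interpretive. It stands in the Conclusions, not the Methods, and names no estimator, so it cannot be said to prescribe a raw point estimate. *Low quit rates* could mean the counselled arm, both arms, or the gain over the brochure, and Section 2.10 promises effect sizes with 95% confidence intervals. A cut-off for *low* may also stand in a full protocol or analysis plan that is not shown. All of this stands, and it limits the point.

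A reader might infer that chance would often condemn a working channel. The documents do not support that as a flat statement, because the frequency runs from about 1% to well over 40% with the reading chosen. If *extremely* is taken to govern quit rates as well as recruitment rates, the counselled-arm risk is about 1% to 17%. The wording places it before recruitment rates only, so milder cut-offs are the more natural reading, but neither is excluded.

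A reader might also infer that the main implementation recommendation would be driven by noise. That goes too far. The process evaluation in Section 2.11 lists recruitment success, calls received, barriers and parents' experiences, not quit rates, and the success criterion in the Conclusions rests on recruitment and cost. Quit rates enter once, as one limb of the condition for dropping a single channel.

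Finally, ignoring quit rates altogether could keep a channel that recruits cheaply but yields few quitters. This is fair, and is why channel quit rates should still be reported. What remains is that the text lets quit rates decide alone, at a level for which the trial was not sized.

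**Conclusion.** The point holds in limited form. The article attaches a firm consequence to channel quit rates, while both the sample size and the planned quit-rate comparisons are at approach level. A channel's counselled quit rate would be known to about ±23 points. Chance alone would produce a visibly low channel anywhere from rarely to in nearly half of trials, depending on a meaning of *low* that is not given. A channel with half the quit rate would be missed in about 61% of trials (100% − 39%).

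These figures assume equal recruitment and the planning rates of 44.5% and 12.1%. Uneven recruitment would leave at least one channel with fewer parents and so less precision. The severity is minor to moderate: the primary comparison, the approach-level analyses and the process evaluation are unaffected.

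**What to change.** In Section 4, remove low quit rates as a sufficient reason for not using a channel. Base channel-level recommendations on recruitment rate and cost per participant, as the preceding sentence already does for success, and keep conclusions about quit rates at approach level. Report each channel's quit rates and its counselling-minus-brochure difference with 95% confidence intervals, labelled descriptive.

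Replacing the quit-rate limb with an interval rule, such as dropping a channel only when its 95% interval excludes the pooled counselling effect, is not recommended. With 18 counselled parents it would pick out a half-as-good channel in only about 21% to 29% of trials, depending on the interval, which is less than the 39% above.

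The cost is wording only: no change to sample size, data or schedule. The downside is a weaker claim about quit rates by channel.
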